### Secondary Outcomes

We will use fNIRS to assess the M1, S1, PMC, and SMA activities during six cycles of 15 s of hand grasping and 45 s of rest while sitting on a reclining chair. Each participant will be assessed at three time points (at baseline, immediately after the 5-week treatment, and at the 3-month follow-up). fNIRS parameters will be assessed and correlations with the clinical outcomes will be assessed. Other secondary outcomes will include activities of daily living, which will be determined using the FIM, and the motor section of FMA-UE will also be used to estimate upper limb movement ability (based on normal reflex activity and volitional movement of the upper extremities, along with the wrist, hand, coordination/speed, sensation, and passive joint motion domains). These stroke-associated measures will be assessed in addition to the primary outcome.

### Statistical Analysis

Statistical analysis will be performed using SPSS 22.0 (SPSS Inc., Chicago, IL, United States). Database management and statistical analysis will be performed by an independent researcher, who will be blinded to group allocation. Monitoring of AEs will be carried out by the treating physical therapists. The primary analysis, which will be a per-protocol analysis, will include the patients who underwent the treatment course and completed the 3-month follow-up.

Descriptive statistics will be used to describe the baseline characteristics of the participants in both groups. The normally distributed continuous data will be presented as mean ± standard deviation, and the non-normally distributed continuous data will be presented as median (maximum and minimum). The Shapiro–Wilk test will be used to evaluate data normality. Homogeneity of variance will be assessed by Levene’s test. For the normally distributed continuous data (including WMFT, UE-FMA, and FIM), paired *t*-tests will be used to compare between baseline and postintervention in each group. Additionally, unpaired *t*-tests will be used to assess the differences in the baseline characteristics and the primary and secondary outcomes between the HTS and sham groups. For the non-normally distributed continuous data, Wilcoxon tests will be used. The one-tailed significance level (α) for statistical hypothesis testing will be set at *P* < 0.025 (Figure 2).

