## Trial Design

This protocol has been designed according to the Standard Protocol Items: Recommendations for Interventional Trials (SPIRIT) guidelines. It is registered with the Chinese Clinical Trial Registry. Based on a 1:1 ratio, 90 participants will be randomly assigned to the HTS and sham groups. The prospective, single-center, double-blind, randomized, sham-controlled clinical trial will study the therapeutic effects of HTS vs. sham intervention. Each patient will undergo 1 session of real/sham HTS per day, always followed by general rehabilitation therapy, 5 days per week, with a total of 25 sessions. Three assessments will be performed in both groups: at baseline, immediately after the 5-week treatment, and at a 3-month follow-up. The effects will be measured using a variety of rating scales. The primary outcome will be the Wolf Motor Function Test (WMFT). The secondary outcomes will be the Fugl-Meyer Assessment for Upper Extremity (FMA-UE), Functional Independence Measure (FIM), and fNIRS parameters. To strengthen treatment compliance and minimize dropout, a doctor will contact the participants regularly.

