## Sample Size Estimation

The calculation of the sample size was based on data from previous research and our per experiment (Lai et al., 2015). As the study involves two groups, the following sample size calculation for a two-sample mean comparison was used:

$$n_{c}=\frac{{\left(Z_{1-\alpha }+Z_{1-\beta }\right)}^{2}\,\sigma^{2}\,\left(1+\frac{1}{K}\right)}{{\left(\mu_{T}-\mu_{C}-△\right)}^{2}}$$

where, Z_1–_*_α_* = 1.960, Z_1–_*_β_* = 0.842, μ_*T*_=6.6 (predicted mean in HTS group); μ_*C*_=2.3 (predicted mean in sham group), σ = 2.0 (standard deviation), *K* = 1 (ratio of participants in the HTS and sham groups), Δ = 3 (optimality bounds), α = 0.025 (2.5% one-tailed significance level), and β = 0.20 (80% power). The calculated required sample size was 37 participants per group. Assuming a 20% dropout rate, 45 participants per group (a total of 90 participants) need to be recruited.

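### The primary analysis is a per-protocol analysis of completers, so the main comparison in this superiority trial is not protected by randomisation

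*Protocol article*

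**What the plan says.** The Statistical Analysis section fixes the primary analysis set: "The primary analysis, which will be a per-protocol analysis, will include the patients who underwent the treatment course and completed the 3-month follow-up".

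The Trial Design section describes a "randomized, sham-controlled clinical trial will study the therapeutic effects of HTS vs. sham intervention", with 1:1 allocation. The Randomization section places allocation after the baseline assessment. Treatment is 25 sessions over 5 weeks, and Table 1 schedules the WMFT at baseline, after treatment and at the 3-month follow-up.

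The Sample Size Estimation section sizes the trial to show HTS better than sham beyond a margin, "Δ = 3 (optimality bounds", with "α = 0.025 (2.5% one-tailed significance level". It ends: "Assuming a 20% dropout rate, 45 participants per group (a total of 90 participants) need to be recruited".

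**The concern.** This is a superiority trial, so there is no non-inferiority aim that could justify giving the per-protocol set first place. Both inclusion conditions arise after randomisation, and either may be related to how the participant is doing.

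Only the HTS arm receives real pulses. The adverse events that the article anticipates (transient arm weakness, soreness, headache, increased arm tone) could both interrupt treatment and affect the WMFT. Arm-specific, outcome-related loss is therefore possible, and the trial's data could not afterwards show that it did not occur. If it did occur, the completer comparison would be biased and the nominal one-sided 2.5% error rate would not hold.

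The rule also discards usable data, because a 5-week WMFT does not count unless the 3-month visit took place.

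**Working it through.** **1. The plan's own figures.** The inputs, all from Sample Size Estimation, are means 6.6 (HTS) and 2.3 (sham), SD 2.0, margin 3, Z values 1.960 and 0.842, and K = 1.

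- Distance beyond the margin: 6.6 − 2.3 − 3 = 1.3.
- n per group = (1.960 + 0.842)² × 2.0² × 2 / 1.3² = 37.17. The plan states 37.
- 37 × 1.20 = 44.4, rounded up to 45, as stated.

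**2. Number excluded.** 20% of 90 is 18, leaving about 36 of 45 per arm. This is not a ceiling. Participants who do not undergo the course but stay in follow-up could be removed as well.

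**3. Bias and error if loss is related to outcome in HTS only.** From the plan: SD 2.0, 45 per arm, 20% loss. Assumed: equal 20% loss in each arm, random loss in sham, and loss in HTS driven by a latent variable with correlation r to poor response. The true difference is set equal to whatever null value is tested.

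- The 20% point of the standard normal is z = −0.842, where the density is 0.280. λ = 0.280 / 0.80 = 0.350.
- Bias = r × 2.0 × λ = 0.70 r.
- Variance among HTS completers = 4 × [1 + r²(zλ − λ²)] = 4 × (1 − 0.417 r²).
- SE = √(variance/36 + 4/36). Error = 1 − Φ(1.96 − bias/SE).

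| r (assumed) | Bias | SE | One-sided error, formula | Bias and error, simulation |
|---|---|---|---|---|
| 0.3 | +0.21 | 0.467 | 6.5% | about +0.2; 6-7% |
| 0.5 | +0.35 | 0.459 | 11.6% | about +0.35; 11% |
| 0.8 | +0.56 | 0.439 | 24.7% | about +0.57; 24% |

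For scale, the plan's whole distance between assumed effect and margin is 1.3.

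**4. Other patterns, same method.**

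- Loss unrelated to outcome: bias 0.00, error about 2.6%.
- r = 0.5 in both arms: bias 0.00, error about 2.4 to 2.7%.
- r = 0.5 in HTS and 0.3 in sham: bias +0.13, error 5.5%.
- Loss of poor responders in sham only, r = 0.5: bias −0.35, error 0.3 to 0.4%.

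**5. How much of this a mixed model removes.** Take r = 0.5 in HTS only and assume a correlation of 0.7 between the 5-week and 3-month scores. A likelihood analysis using the 5-week scores leaves about +0.18 to +0.19 of the +0.35 if every loss comes after week 5. It leaves +0.26 if half do, and essentially all of it if none do.

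**6. Power with all 45 per arm analysed, margin of 3 tested.** Assume a fraction d of HTS participants do not complete and gain only the sham mean.

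- Difference = 4.3 × (1 − d): 4.09, 3.87 and 3.44 for d = 5%, 10% and 20%.
- SE with SD 2.0 = 2.0 × √(2/45) = 0.422. Power = Φ((difference − 3)/0.422 − 1.96) = 73%, 54% and 18%.
- Allowing for the larger SD of a mixed HTS arm gives about 69%, 47% and 14%.
- With no dilution, 45 per arm gives 87%, against 79% with 36 per arm.

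**The case against.** The strongest objection is that a reader might infer from step 3 that the plan's error rate is inflated, and in favour of HTS. The documents do not support that. They give no loss by arm, and 20% is a planning allowance. The sham coil is matched for appearance, sound and feel, and the equipment displays are identical, so lack of perceived benefit may act alike in both arms. Step 4 shows that this gives no bias, and that the reverse pattern hurts HTS. The article also calls peripheral magnetic stimulation painless and well tolerated, and it plans regular phone contact to limit dropout. All of this stands, and the figures are illustrations only.

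The error figures also depend on which null is tested. The sample size uses a margin of 3, while Statistical Analysis names an unpaired t-test without saying whether the margin enters. Against that margin, a treatment with no effect would almost never be declared superior. The figures apply when the true difference equals the tested null value, whichever that is.

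Much of the illustrated bias comes from missing outcomes, which a change of analysis set cannot fully cure (step 5). That stands too, and is why the fix includes continued assessment and a sensitivity analysis.

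A reader might also infer that no all-randomised analysis exists at all. The article is a condensed account, so its silence carries no weight here. The per-protocol set, however, is not an omission: it is stated outright as primary.

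**Conclusion.** The point stands as a fault in a stated choice. The primary analysis set is defined by two post-randomisation events in a randomised superiority trial, and it drops participants who have valid 5-week scores. To say that randomisation is broken would go too far: allocation is sound, but the primary comparison no longer has its protection.

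About 18 of 90 participants would be excluded at the planned dropout, possibly more. Bias is a risk of unknown direction and size. It could be zero, or a substantial part of the 1.3 points on which the sample size rests. The numerical illustrations rest on the plan's SD, sample size and dropout, and on loss patterns that are assumed.

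**What to change.** - Define the primary analysis as all randomised participants in their assigned group. Use every available 5-week and 3-month WMFT score with baseline WMFT as covariate, for example in a mixed model for repeated measures, and name the visit that carries the primary contrast.
- Continue outcome assessment of participants who stop stimulation.
- Add a sensitivity analysis for outcome-related missingness, since the mixed model removes only part of that bias.
- Keep the per-protocol set as a supportive analysis.

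**Cost.** This is a change of analysis wording plus a change in conduct: those who stop stimulation must still be followed. Recruitment had already begun by the date of the protocol version. The expected effect is smaller than among completers. If the margin of 3 is the null tested, power could fall materially (step 6), so the sample size should be rechecked against the new primary analysis.

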## Eligibility Criteria

The inclusion criteria are as follows:

(1) Having a first unilateral supratentorial, ischemic stroke, and having had a stroke in 4–12 month;

(2) Upper extremity dysfunction, with FMA-UE motor score of 30–60 out of 66 (Fugl-Meyer et al., 1975);

(3) Aged 18–80 years, regardless of sex;

(4) Mini Mental State Examination (MMSE) score > 24;

(5) Written informed consent;

(6) Right handedness.

The exclusion criteria (based on the TMS safety criteria proposed by Wassermann, 1998) are as follows:

(1) Metal implant device in the head, neck, or stimulation area;

(2) Medical implant device (cardiac pacemaker or cochlea implant);

(3) Pregnancy;

(4) Current or history of epilepsy;

(5) Current or history of medications known to affect central nervous system excitability;

(6) Intracranial hypertension;

(7) Unstable fractures or joint contracture.

(8) Taking drugs that may increase the risk of epilepsy or reduce cortical excitability.

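### The planned between-arm t-tests make no stated use of the baseline scores collected in every participant; baseline-adjusted analysis would gain precision at no data cost, and the within-arm tests should be marked descriptive

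*Protocol article*

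**What the plan says.** The Statistical Analysis section lists two kinds of comparison for continuous outcomes, naming WMFT, FMA-UE and FIM. First, within each arm, paired t "tests will be used to compare between baseline and postintervention in each group". Second, unpaired t-tests "will be used to assess the differences in the baseline characteristics and the primary and secondary outcomes between the HTS and sham groups". Normality is checked with the Shapiro–Wilk test, and Wilcoxon tests are used where it fails. The section names no covariate and no model, and it does not say whether the unpaired test is applied to post-treatment scores or to changes. Nor does it say which of the two kinds of comparison decides efficacy.

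Table 1 (Assessments) schedules WMFT, FMA and the functional independence scale at baseline, after treatment and at follow-up, so baseline values should exist for every participant. The entry criterion is broad: "Upper extremity dysfunction, with FMA-UE motor score of 30–60 out of 66".

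The Sample Size Estimation section plans a two-sample comparison of means with "6.6 (predicted mean in HTS group"), "2.3 (predicted mean in sham group), σ = 2.0 (standard deviation"), "Δ = 3 (optimality bounds") and "α = 0.025 (2.5% one-tailed significance level), and β = 0.20 (80% power"). It does not name the scale or say whether the means are scores or changes. The analysis section uses the same level: "The one-tailed significance level (α) for statistical hypothesis testing will be set at" 0.025.

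**The concern.** A participant's arm function after treatment depends heavily on where that participant started, and the entry range admits very different starting points. An unadjusted comparison of scores puts that spread into the error term and lets a chance difference between arms at baseline pass into the estimate. A comparison of changes removes part of the spread but over-corrects when the correlation is below 1. Adjusting for baseline is at least as precise as either, and the data are already being collected.

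The paired tests raise a separate matter of interpretation. A test of change within one arm mixes any treatment effect with recovery, conventional rehabilitation, practice and regression to the mean. Both arms receive conventional rehabilitation. With paired and unpaired results listed side by side and no statement of which one counts, a report could present a significant change in the HTS arm as if it were evidence for HTS.

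Letting a normality test choose between the t-test and the Wilcoxon test also means that the form of the primary test is not fixed in advance.

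**Working it through.** **Inputs from the protocol article.** Planned means 6.6 and 2.3, SD 2.0, margin 3, one-sided 0.025, 80% power, 37 per arm, 45 per arm recruited, 20% dropout (Sample Size Estimation); 17 tasks scored 0 to 5 (Primary Outcomes). **Assumed, because not given:** correlation r between baseline and follow-up of 0.5 to 0.9, and equal variance at the two visits.

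**1. The plan's own figure.** n = (1.960 + 0.842)² × 2.0² × 2 / (6.6 − 2.3 − 3)² = 7.851 × 4 × 2 / 1.69 = 37.17. The stated 37 is reproduced (38 if rounded up). After 20% loss, 45 × 0.8 = 36 per arm remain, which is used below.

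**2. What the planning means can be.** The maximum total is 17 × 5 = 85. A mean of 6.6 exceeds the item maximum of 5, and as a total it is 6.6/85 = 8% of the scale, in patients with 30/66 = 45% to 60/66 = 91% of the FMA-UE maximum. The values look like changes, but the section does not say so. Both readings are therefore carried forward.

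**3. Variance of the between-arm difference.** With score variance σ² and n per arm:
- t-test on post-treatment scores: 2σ²/n
- t-test on changes: 2 × 2σ²(1 − r)/n
- ANCOVA: 2σ²(1 − r²)/n

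Excess variance over ANCOVA is 1/(1 − r²) − 1 for scores and 2/(1 + r) − 1 for changes.

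| r | scores | changes |
|---|---|---|
| 0.5 | 33% | 33% |
| 0.7 | 96% | 18% |
| 0.8 | 178% | 11% |
| 0.9 | 426% | 5% |

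**4. Power at the plan's own net difference.** Using 1.3, SD 2.0, 36 per arm and the normal approximation, the unadjusted test has 78.7% power. If SD 2.0 belongs to the change, ANCOVA multiplies the SD by √((1 + r)/2) and gives 89.0%, 84.9%, 82.8% and 80.8% at r = 0.5, 0.7, 0.8 and 0.9. If SD 2.0 belongs to the score, it multiplies the SD by √(1 − r²) and gives 89.0%, 97.1%, 99.6% and over 99.9%.

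**5. Chance imbalance.** The standard error of the baseline difference is σ√(2/36) = 0.24σ. At r = 0.8, an imbalance of that size shifts a comparison of scores by 0.8 × 0.24σ = 0.19σ, and a comparison of changes by 0.2 × 0.24σ = 0.05σ in the opposite direction. ANCOVA removes both.

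**6. The within-arm test when HTS adds nothing.** Suppose 2.3 is a change and both arms change by 2.3. The expected paired t with 36 participants is 2.3/(SD/√36).

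| assumed SD of change | expected t | HTS arm significant | HTS significant, sham not |
|---|---|---|---|
| 2.0 | 6.9 | about 100% | about 0% |
| 4 | 3.5 | 92% | 7.5% |
| 6 | 2.3 | 61% | 24% |
| 8 | 1.7 | 39% | 24% |

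The third column is p from the noncentral t at one-sided 0.025; the fourth is p(1 − p). The between-arm test rejects in about 2.5% of such trials.

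**The case against.** The strongest reply is that the plan already contains the right kind of comparison. It has a randomised between-arm test of the primary outcome, the trial is sized on a two-sample comparison, and nothing in the text makes the paired tests the basis for efficacy. That stands. A reader might infer that the trial will declare HTS effective from the paired tests. The document does not say this; it only fails to rule it out.

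A reader might also infer that the planned test cannot have the SD used for power. That follows only if post-treatment scores are compared, which the text leaves open. Under that reading, with an assumed score SD of 8 to 12, a difference of 4.3 tested against zero and 36 per arm, the unadjusted test has 61% to 32% power, against 96% to 71% for ANCOVA at r = 0.8. This is the worst case. On the same inputs a t-test on changes has 94.5% to 65.9% at r = 0.8 and 99.9% to 91.8% at r = 0.9; ANCOVA has 96.3% to 70.5% and 99.9% to 93.1%. The gain is then about 0 to 5 points. These figures also ignore the margin of 3.

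Nor can the largest figures be combined. A change SD of 2.0 with a score SD of 8 to 12 implies r = 1 − 2.0²/(2 × 8²) = 0.97 to 1 − 2.0²/(2 × 12²) = 0.99, not 0.8 or 0.9. At r = 0.8 to 0.9 and those score SDs, the change SD is 3.6 to 7.6, and a significant result within the sham arm is not a near certainty.

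On the normality test, the section itself lists WMFT, FMA-UE and FIM as normally distributed, so the switch to Wilcoxon may never occur. The wording still allows it.

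**Conclusion.** The point holds as an improvement that should be made, not as an error that invalidates the analysis. The unadjusted between-arm test is unbiased under randomisation. It is less precise than ANCOVA under either reading of the outcome, and it is exposed to chance baseline imbalance. How much is lost depends on a correlation the protocol does not give and on a choice it does not state. If changes are compared, which the planning values suggest, the cost is modest: 33% down to 5% excess variance for r of 0.5 to 0.9. If post-treatment scores are compared, it is 33% up to 426%.

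That a within-arm improvement is not evidence of a treatment effect holds as a matter of design. The rates calculated for it depend on reading 2.3 as a change under sham and on the assumed SD of change.

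**What to change.** State in the Statistical Analysis section that the primary comparison is an ANCOVA, or a repeated-measures mixed model, of WMFT with treatment and baseline WMFT as terms. Report the adjusted HTS minus sham difference with its 95% confidence interval, whose two-sided level matches the one-sided 0.025, and make it the sole basis for efficacy. With baseline as a covariate, ANCOVA gives the same treatment difference whether the response is the score or the change, so the present ambiguity no longer matters.

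Analyse FMA-UE and FIM in the same way. Label the within-arm changes descriptive. Fix the primary method in advance and keep the Wilcoxon test as a sensitivity analysis, so that the Shapiro–Wilk result does not select the primary test.

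The cost is a wording change. Because recruitment has already begun, it should be a dated amendment made before unblinding. No new data or visits are needed.

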**FIGURE 2 F2:**
[figure not shown]
Overview of study design.

## Discussion

Limb motor function is controlled by neural networks in several brain regions, including the default mode network and the sensory and motor networks. The motor network includes M1, pyramidal system, supplementary motor cortex (SMA)/PMC, parietal temporal cortex, basal ganglia, and cerebellum. Sensory information is integrated through the parietal temporal cortex and then connected to the brain motor neural circuits *via* a special network. Both human and animal studies have shown that the brain areas surrounding stroke lesions can promote motor function recovery (Payne and Lomber, 2001). The non-injured areas around the lateral hemisphere after stroke have a certain degree of plasticity, likely due to the reorganization of sensorimotor networks.

This plasticity may depend on the functional overlapping regions in the sensorimotor network, which may compensate for the lost function after stroke. A study suggested a surrogate role for the SMA after M1 injury in monkeys. Before M1 injury, SMA neurons exhibited activity during learning (push-button task), which disappeared when performing the task after the task had been learnt. However, M1 injury led to SMA activity being restored when the task was performed again (Williams et al., 2006). This phenomenon is consistent with the ipsilesional SMA activation in stroke patients during rehabilitation (Hara, 2015). Zhang et al. (2016) found that compare to the health control functional connections between M1 and the ipsilesional parietal cortex, frontal gyrus, and SMA were increased in chronic stroke patients, while functional connections between bilateral M1 were decreased in stroke. Inman et al. (2012) found that the connections between the superior parietal cortex and M1, and the superior parietal cortex and the SMA, were significantly reduced in chronic stroke. The study of Jingchun et al. (2020) used fine map of fMRI showed that he CST originated from SMA are significantly related with motor outcomes in chronic stroke patients. The SMA/PMC is the key area for motor plan formation and movement initiation. The SMA/PMC and the prefrontal cortex form the brain’s cognitive network, which predicts the movements needed for tasks to be performed and receives information from the brain’s sensory integration network about the body’s spatial location, generating a primary task plan. Our study aims to restore the motor circuits, based on the ideas of Donald Hebb. He hypothesized that when the axon of cell A repeatedly or continuously participates in stimulating cell B, the synaptic connection between cell A and cell B will be strengthened. On this basis, Muming Poo found that long-term potentiation or depression can be produced by exciting the postsynaptic membrane 20 ms after or before exciting the presynaptic membrane, respectively, which is known as spike timing-dependent plasticity. The difference between spike timing-dependent plasticity and Hebbian theory is that the former emphasizes the role of the sequence of presynaptic and postsynaptic membrane excitation in synaptic remodeling (Zuzanna et al., 2019).

There is a lack of guidelines on PAS HTS for stroke rehabilitation in the subacute and chronic phases. Our planned study may complement the existing stroke rehabilitation guidelines, add to the experience in this area, and provide a basis for treatment application.

